### Data analysis

We will use SPSS 22.0 for Windows to perform a statistical analysis. Descriptive statistics and means will be used to describe the participants’ background information and clinical variables. Poisson regression will be used to examine the mean difference for the hospital readmission rate between groups. A generalized estimating equation (GEE) will be used to examine the group, time, and interaction effects on the secondary outcome variables. The GEE is chosen because it treats observations of longitudinal data as correlated and thus is more robust in estimating standard errors [68].

The final report will follow the Consolidated Standards of Reporting Trials (CONSORT) statement as well as its extension for non-pharmacological interventions/complex intervention.

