## Background

Heart failure (HF) is a global health issue affecting more than 5 million people in the United States (US) [1] and 14 million Europeans [2]. In Hong Kong, the overall HF ratio per 1,000 people is 0.7, resulting in a total of over 5,000 cases; the new:old case ratio is 2.8:1 [3]. Heart failure is the leading cause of death in the US, accounting for 31.4 % of all deaths and followed by cancer and stroke [4]. In Hong Kong, cancer is still the leading cause of death (30.6 %), but heart disease was ranked second (15.5 %) among the 42,705 deaths in 2009 [5]. The management of HF in recent years has improved, but the mortality rate remains high, with a reported 40 % death rate within the first year after diagnosis [6, 7] and 75 % at five years [8]. Patients with heart failure tend to need more emergency room visits, repeated hospital admissions, and longer lengths of stay [1]. In Hong Kong, around 25–50 % of HF patients are readmitted within 6 months of discharge [9]. The repeated use of services results in increased healthcare expenditures [10, 11], costing US$30 billion a year in the US [1] and GBP 905 million in the United Kingdom [8].

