The prognosis for patients with HF is poor, and various burdens become prominent when HF progresses to the end stage. End-stage heart failure is resistant to medical therapy [1], and this group of patients experiences a marked reduction in health-related quality of life [6, 12], encountering health problems encompassing physical, psychological, social, and spiritual aspects. Topping the list of physical symptoms are fatigue, dyspnea, and edema [6, 12, 13]. Other reported symptoms include decreased appetite, cough, dry mouth, and pain [6, 12]. With their progressive decline in functional status, these patients often have increasing difficulty dealing with daily activities [14, 15]. Psychologically, some patients with HF live in the shadow of fear [16], experiencing emotional turbulence [17] and feeling frustrated with their sense of personal failure [18]. Patients show symptoms of insomnia, worry, sadness, and irritability [6, 12]. Socially, patients with HF feel isolated and lonely [14, 19–21], often relying on others for daily living assistance and thus regarding themselves as a burden to their carers [19]. These patients also face spiritual issues, such as questioning the meaning of living with severe HF as they experience strong feelings of uncertainty and hopelessness [20]. In fact, patients understand that their condition could change rapidly, including a sudden decline resulting in death [20, 22]. Apart from the symptom burden, heart failure also imposes a financial burden on the healthcare system, particularly in the form of hospital readmission [23, 24]. Heart failure is a leading cause of hospitalization, and a systematic review confirmed that about 25 % of patients hospitalized with HF are readmitted within 30 days [23]. Reasons for hospital readmission were worsening of symptoms, unavoidable progression of illness, distressing psychosocial issues, inadequate self-care adherence, and lack of knowledge on how to seek help from the healthcare provider [24, 25]. Therefore, it is essential to address end-stage HF patients’ physical, psychological, and spiritual needs in order to facilitate a better hospital-to-home transition for them.

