Therefore, we designed the present study aiming to compare the effects of customary hospital-based care and an interventional Home-based Palliative HF Program (HPHP). Our objective is to examine the effect of the HPHP on hospital readmission rate, quality of life, functional status, symptom intensity, and satisfaction with care. The key outcome of this study is the hospital readmission rate, and the primary endpoint is 4 weeks post-discharge. The hypothesis is that patients with end-stage heart failure (ESHF) receiving the HPHP will have a lower hospital readmission rate than those receiving customary hospital-based care at 4 weeks post-discharge.

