### Study settings and participants

This is a multisite study conducted in collaboration with the palliative care teams from three regional hospitals. In-hospital patients with ESHF are reviewed by the physicians, and patients who are seen to be not benefiting from active medical treatment are considered for palliative care. The general inclusion criteria for subject recruitment include the ability to speak Cantonese, living within the hospital service area, and the ability to be contacted by phone. Specific inclusion criteria are based on the National Gold Standards Framework, Prognostic Indicator Guidance 2008 [51], in which patients must fulfill at least two of the indicators: (i) HF with New York Heart Association stage III or IV, (ii) patient thought to be in the last year of life, (iii) repeated hospital admissions with symptoms of HF, (iv) existence of physical or psychological symptoms despite optimal therapy. The nurse who is responsible for recruitment identifies eligible subjects, and the physician confirms that the patient fulfills the specific criteria and refers him/her to the PC team. Those with cognitive impairment, diagnosed with severe psychiatric disorders in their medical record, or discharged to a nursing home or other institution are excluded.

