### Secondary outcomes

Evaluated health outcomes will be functional status, symptom intensity, and satisfaction with care. Functional status will be measured by the Palliative Performance Scale (PPS). The PPS, developed by Anderson et al. [61] based on the Karnofsky Performance Scale, is a tool specifically designed for palliative patients that reflects the changing physical condition in five aspects: ambulation, activities/evidence of disease, self-care, intake, and level of consciousness. The PPS is a clinical tool commonly used in local settings. The level of physical performance is rated on a scale of 100 (normal) to 0 (death), measured in 10 % decrement levels. The scale has been validated and the inter-rater reliability between doctors and nurses was maintained at .85 with strong kappa values of .97 [62]. The internal consistency is also good, with a Cronbach’s alpha equal to 0.83 [63].

The symptom intensity will be measured by the Edmonton Symptom Assessment System (ESAS). The ESAS assesses nine symptoms: pain, fatigue, nausea, depression, anxiety, drowsiness, appetite, sensation of well-being, and dyspnea, measured on a 0–100 mm visual analog scale (VAS). One extra empty VAS is left for the assessment of a less frequent symptom that may be important for an individual patient. The ESAS is widely adopted locally, and has been found to be a valid, reliable instrument for use among palliative care patients [64, 65]. A local study has also shown that the ESAS can help quantify symptoms and is an independent prognosticator for survival [66].

Satisfaction with care will be measured by the 15-item questionnaire used in the study of Wong et al., with validity confirmed by an expert panel and a reported test-retest reliability of .87 [42].

The service utilization outcome is measured by the hospital readmission rate, length of stay, and emergency room visits. The information will be extracted from the hospital administrative systems.

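### The readmission comparison is stated with no baseline term; adding pre-index admissions would be a cheap gain in precision, small at 4 weeks and larger over longer windows

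*Protocol article*

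**What the plan says.** All from the protocol article.

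- **Model for readmission** (Data analysis): "Poisson regression will be used to examine the mean difference for the hospital readmission rate between groups". No covariate or stratum is named.
- **Model for the other outcomes** (Data analysis): "A generalized estimating equation (GEE) will be used to examine the group, time, and interaction effects on the secondary outcome variables". Here the section does list model terms.
- **Entry criteria** (Study settings and participants): "patients must fulfill at least two of the indicators", and the third of the four reads "iii) repeated hospital admissions with symptoms of HF". A patient can therefore qualify with or without a history of repeated admission.
- **Data source** (Secondary outcomes), for readmission, length of stay and emergency room visits: "The information will be extracted from the hospital administrative systems".
- **Standing of readmission** (Background): "The key outcome of this study is the hospital readmission rate, and the primary endpoint is 4 weeks post-discharge". The Abstract and the Primary outcome section make quality of life primary instead. That conflict is a separate matter, but readmission is important on either reading.
- **Allocation** (Randomization and blinding): permuted blocks, with no stratification by admission history described.

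**The concern.** Earlier hospital use is a natural predictor of later hospital use, and the article's own entry criteria treat it as a marker of prognosis. Because any two indicators suffice, the trial can mix frequent and infrequent users of hospital care. If the model contains only group, the variation between patients that their history could explain stays in the error of the rate ratio.

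Earlier admissions precede randomization, so neither arm's care can affect them and adjusting for them is safe. The only stated hypothesis concerns readmission, while the sample size rests on quality of life. No power was planned for readmission, so precision there has no stated reserve.

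**Working it through.** **The plan's own figure.** There is none to reproduce: the article gives no effect size, power or sample size for readmission. The 117 per arm (140 after attrition) come from quality of life and serve here only as group sizes.

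**Inputs from the article**
- "about 25 % of patients hospitalized with HF are readmitted within 30 days". Under a Poisson model this is −ln(1 − 0.25) = 0.288 events per patient, taken as the 4-week mean.
- "around 25–50 % of HF patients are readmitted within 6 months of discharge". The upper end gives −ln(1 − 0.50) = 0.693 events in 6 months, or 1.386 in 12 months at a constant rate.

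**Assumptions, not in the article:** rate ratio RR = 0.65; between-patient variance k = 0.5 to 1.0; share of that variance explained by earlier admissions r² = 0.10 to 0.50; full exposure; 117 per arm; two-sided 0.05.

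**Formula**
- Without a baseline term: Var(log RR) = [1/μ + 1/(μ·RR) + 2k]/n.
- With one: replace k by k(1 − r²).
- Proportional reduction: 2k·r² / [1/μ + 1/(μ·RR) + 2k].

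**Worked case: 4 weeks, k = 1.0, r² = 0.50**
- 1/μ = 3.476 and 1/(μ·RR) = 5.348, sum 8.824. Adding 2k gives 10.824.
- Reduction = 1.0/10.824 = 9.2%.
- Standard error: √(10.824/117) = 0.304 without the term and √(9.824/117) = 0.290 with it.
- With |ln 0.65| = 0.431, power is Φ(0.431/0.304 − 1.96) = 0.293 without and Φ(0.431/0.290 − 1.96) = 0.318 with.

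**Corners of the range** (variance reduction; power without → with)

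| Control mean | k 0.5, r² 0.10 | k 0.5, r² 0.50 | k 1.0, r² 0.10 | k 1.0, r² 0.50 |
|---|---|---|---|---|
| 0.288 | 1.0%; 0.318→0.321 | 5.1%; 0.318→0.332 | 1.8%; 0.293→0.298 | 9.2%; 0.293→0.318 |
| 0.693 | 2.1%; 0.578→0.588 | 10.7%; 0.578→0.627 | 3.5%; 0.499→0.513 | 17.7%; 0.499→0.578 |
| 1.386 | 3.5%; 0.791→0.805 | 17.7%; 0.791→0.863 | 5.2%; 0.663→0.686 | 26.1%; 0.663→0.791 |

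**Simulation** (gamma-Poisson patients, Poisson regression with robust variance, 1,500 trials per setting)

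1. 140 per arm, assumed mean of 2 earlier admissions, covariate log(1 + count), k = 0.3, 0.5, 1.0.
   - 4 weeks (mean 0.25): the standard deviation of log RR goes from 0.292 to 0.291, 0.288 to 0.284 and 0.311 to 0.296. Since 1 − (0.291/0.292)² = 0.7% and 1 − (0.296/0.311)² = 9.4%, the reduction is about 1–9%.
   - 12 months (assumed mean 2): 0.113 to 0.105, 0.120 to 0.106 and 0.151 to 0.118, a reduction of 14–39%. At an assumed RR of 0.75, power rises from 73/64/46% to 80/76/70%.
   - With only a yes/no history (two or more earlier admissions), the reduction is 0–4% at 4 weeks and 9–23% at 12 months.
2. 117 per arm, earlier mean 1.386, covariate log(count + 0.5), RR 0.65, k = 0.5 and 1.0.
   - Mean 0.288: reduction 4.5% and 12%; power 0.334→0.349 and 0.279→0.299.
   - Mean 1.386: reduction 13% and 31%; power 0.788→0.838 and 0.653→0.817.
   - Under no effect, type I error was 0.053–0.063 with and without the term. Mean estimates hardly differed (for example −0.446 and −0.447).
3. At a lower later mean of 0.8, the reduction was 5–27%.

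The 12% in the second simulation exceeds the table's 9.2% because a count with mean m explains mk/(1 + mk) of the between-patient variance in this model. For m = 1.386 and k = 1 that is 1.386/2.386 = 0.58, above the 0.50 cap used in the table.

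**The case against.** **Silence is not a decision.** The sentence does not say that the model is unadjusted, and covariate lists are commonly left to a full protocol or analysis plan, neither of which is shown. A reader might infer that the trial has rejected adjustment; the article does not support that. What stands is narrower: the model as stated is a comparison between groups with no baseline term, in a section that does list terms for the other model, and a specific pre-randomization covariate would improve it.

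**The covariate may not be on file.** A reader might infer that every patient's earlier admissions are recorded at entry and stored alongside the outcome. The article does not show this. The indicator is qualitative and limited to HF symptoms, and a patient may qualify on two others. The administrative systems are described only as a source of outcome data. The objection stands, so the fix needs a fallback.

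**Little is gained where the hypothesis sits.** This also stands. At 4 weeks counts are small and Poisson noise dominates. Using the first simulation's standard deviations and RR = 0.75, power moves from about 16.5 to 16.6%, 16.8 to 17.2% and 15.0 to 16.2%.

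**The longer-window figures are generous.** A 12-month mean of 2 is an assumption at the high end, and deaths would shorten exposure in patients thought to be in their last year of life. Fewer events bring the gain back towards the 4-week figures.

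**Chance imbalance.** If 30–50% of patients have repeated admissions, the standard error of the difference in that share between arms is √(2p(1 − p)/140) = 0.055 to 0.060, so a gap of 10 points or more occurs in about 7–9% of randomizations. A reader might count this as a further harm or as bias. It is neither: randomization balances the history in expectation, and the standard error already carries the chance part.

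**Conclusion.** The point holds as a modest matter of precision. The unadjusted analysis is not wrong, and no figure in the article changes.

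- **4 weeks:** roughly 1–9% less variance of the log rate ratio (12% in the most favourable simulation), worth about 0 to 2 power points, or 2.5 at the best corner of the table.
- **Longer windows:** roughly 5–39% less variance across the simulations. If history explains only a tenth of the between-patient variance, the table gives 2.1–5.2%.

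These sizes rest on assumed rate ratios, between-patient variance, explanatory share, admission rates and full exposure. The 4-week and 6-month rates are background figures for HF patients generally, not for this end-stage population. The direction does not depend on these choices, provided that earlier admissions predict later ones, as the entry criteria imply.

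**What to change.** Before the arms are compared, state in Data analysis (or in the analysis plan) that:

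1. the readmission model contains treatment group plus hospital admissions in the 12 months before the index admission, entered as log(1 + count), if the administrative extract provides them;
2. otherwise it contains the repeated-admission indicator as recorded at screening;
3. the same covariate is used for emergency room visits and length of stay;
4. the unadjusted rate ratio is reported as a sensitivity analysis.

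The look-back window and the source should be fixed at the same time. The Trial status section puts data collection at its final stage, and an adjustment chosen after the arms have been seen would be open to challenge.

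The cost is a short addition to the analysis text and one extra field in the extract, with no new patients or visits. The return at the 4-week endpoint is small; the main benefit is for readmission and service use over longer follow-up.

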**Methods/design:**

This is a randomized controlled trial taking place in hospitals in Hong Kong. We have been recruiting patients with end-stage HF who are identified as appropriate for palliative care during hospitalization, on referral by their physicians. A set of questionnaires is collected from each participant upon discharge. Participants are randomized to receive usual care (customary hospital-based care) or the intervention (HPHP). The HPHP will be implemented for up to 12 months. Outcome measures will be performed at 1, 3, 6, and 12 months post-discharge. The primary outcome of this study is quality of life measured by the Chronic Heart Failure Questionnaire - Chinese version; secondary outcomes include readmission rate, symptom intensity, functional status, and satisfaction with care.

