### Outcome measures

Data for the outcome measures will be collected at five time points: at discharge and at 1, 3, 6, and 12 months post-discharge. A research assistant with no clinical association with the patients will be responsible for collecting the data. In order to ensure the quality of the data collected, the research assistant will be trained in using different data collection tools. A value of 10 % will be used to test the intra-rater reliability, which involves the assistant collecting the same set of data twice within a short interval of time. All the data is independently checked by a member not involved in data collection to ensure the quality of the data collected. All data will be stored in a locked cabinet and will be entered in encrypted files to ensure data protection.

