### Primary outcome

The primary outcome is quality of life, which will be measured by an HF-specific scale, the Chronic Heart Failure Questionnaire - Chinese version (CHQ) at 4 weeks post-discharge. The CHQ is one of the most commonly used HF-specific QOL instruments. It was developed by Guyatt et al. [58] in Canada. The tool has 20 items on a 7-point Likert scale measuring four domains: dyspnea, fatigue, emotional status, and mastery. The CHQ has been translated into Chinese and validated [59]. The internal consistency and test-retest reliability are good, with a Cronbach’s alpha of 0.95 and an intra-class correlation coefficient (ICC) of 0.75 [59]. In addition, the quality of life will also be measured by the McGill Quality of Life Questionnaire - Hong Kong version (MQOL-HK), which is a palliative-specific instrument measuring four domains: physical, psychological, existential, and support on a numerical scale from 0 to 10. It has been validated among palliative patients in Hong Kong with good reliability (the ICC is 0.85 (*p* < 0.0001) and the Cronbach’s alpha is 0.83) [60].

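### The methods listed under Data analysis leave the stated primary outcome, CHQ at 4 weeks, without a test, and no GEE term is named as decisive

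*Protocol article*

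**What the plan says.** The protocol article describes the primary outcome in two ways.

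- **Quality of life.** The Abstract states: "The primary outcome of this study is quality of life measured by the Chronic Heart Failure Questionnaire - Chinese version", and lists readmission among the secondary outcomes. The Primary outcome section agrees ("The primary outcome is quality of life, which will be measured by an HF-specific scale") and fixes the time: "Chinese version (CHQ) at 4 weeks post-discharge". Sample size estimation uses a quality-of-life difference, 60.4 against 52.3. The Secondary outcomes section covers function, symptoms, satisfaction and service use; CHQ is not there.
- **Readmission.** The last paragraph of the Background states: "The key outcome of this study is the hospital readmission rate, and the primary endpoint is 4 weeks post-discharge". The only hypothesis given is that patients on the programme "will have a lower hospital readmission rate than those receiving customary hospital-based care at 4 weeks post-discharge".

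Data analysis names two inferential methods. The first is for readmission: "Poisson regression will be used to examine the mean difference for the hospital readmission rate between groups". The second is a GEE, which "will be used to examine the group, time, and interaction effects on the secondary outcome variables". The visits come from the Outcome measures section: "Data for the outcome measures will be collected at five time points: at discharge and at 1, 3, 6, and 12 months post-discharge".

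**The concern.** An outcome that is called primary and that determines the sample size should have one identifiable test. Here the analysis section covers readmission and the secondary variables, and CHQ is neither under the Abstract and the Primary outcome section.

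Assuming that CHQ simply goes through the GEE does not settle the matter. That sentence offers three effects (group, time, interaction) over five visits, one of which is discharge, before the post-discharge programme could have acted. The endpoint is a single visit, 4 weeks. The terms answer different questions and can disagree, so with none designated the choice could be made after the results are seen. The Trial status section says that data collection is in its final stage, so little time remains to fix the choice in advance.

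**Working it through.** **Step 1: match outcomes to methods.**

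| Reading | Primary | Test of the primary in Data analysis |
|---|---|---|
| Abstract; Primary outcome | CHQ (at 4 weeks in the latter) | None: Poisson is for readmission, GEE for secondary variables |
| End of Background | Readmission at 4 weeks | Poisson regression; CHQ would then fall under the GEE |

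Data analysis sets readmission apart from the secondary variables. This fits the Background and contradicts the Abstract, where readmission is itself secondary. The mismatch is therefore most simply explained by two versions of the primary outcome.

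**Step 2: what the GEE could deliver for CHQ.** With time as a category and discharge as the reference, the month-1 group-by-time coefficient is the between-group difference in change from discharge to 4 weeks (taking the 1-month visit as the 4-week visit). The required contrast is inside the model, but the text does not single it out.

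**Step 3: how much the choice of test matters (illustration only).**

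Inputs from the article: difference 60.4 − 52.3 = 8.1; 117 per arm for 80% power at 0.05; 140 per arm after the attrition allowance, of whom 140 × 0.8 = 112 remain at 20% loss.

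Not stated: SD, sidedness, and the correlation r between baseline and 4-week CHQ. The stated 117 can therefore be neither confirmed nor refuted. Solving backwards for a two-sided test:

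- normal approximation: d = (1.960 + 0.842) × √(2/117) = 0.366, so SD = 8.1/0.366 ≈ 22.1;
- t-test: d = 0.368, SD ≈ 22.0.

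I use 0.368 below; 0.366 changes the results by less than one percentage point. (One-sided, the normal approximation gives d ≈ 0.325.)

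Power ≈ Φ(d√(n/2)/f − 1.960). With n = 112, d√(n/2) = 0.368 × 7.483 ≈ 2.753. The factor f is 1 for the unadjusted 4-week comparison, √(1 − r²) adjusted for baseline, and √(2(1 − r)) for the change score.

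| r (assumed) | Unadjusted | Adjusted for baseline | Change score (month-1 coefficient) |
|---|---|---|---|
| 0.3 | 79% | 82% | 64% |
| 0.5 | 79% | 89% | 79% |
| 0.6 | 79% | 93% | 87% |

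Example at r = 0.5, adjusted: 2.753/0.866 = 3.178; 3.178 − 1.960 = 1.218; Φ = 0.89.

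**Step 4: the omnibus terms.** Assume r = 0.5 between all visits, no missing data, the interaction tested on 4 df, and the group effect read as the average over five visits.

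- Interaction: non-centrality = n/(2(1 − r)) × Σ(eᵢ − ē)², where eᵢ is the effect at visit i in SD units, zero at discharge.
- Group effect: ē divided by its standard error √((1 + 4r)/5 × 2/n) = √(0.6 × 2/112) = 0.1035.

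| True effect over the four follow-up visits (multiples of d) | Interaction | Group effect |
|---|---|---|
| Sustained: 1, 1, 1, 1 | 81% | 81% |
| Waning: 1, 0.75, 0.5, 0.25 | 69% | 43% |
| 4 weeks only: 1, 0, 0, 0 | 81% | 11% |
| Month 12 only: 0, 0, 0, 1 | 81% | 11% |

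The sustained, 4-week-only and month-12-only patterns all have Σ(eᵢ − ē)² = 0.8d², so non-centrality = 112 × 0.8 × 0.368² ≈ 12.1. In the last row nothing happens at 4 weeks, yet the interaction is significant four times in five.

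**The case against.** The strongest reply is that a CHQ analysis is almost certainly intended. Read with the Background, Data analysis is coherent: Poisson for readmission, GEE for everything else, CHQ included. On that view the fault is one of labelling. This stands as an account of the cause. It does not remove the fault, because the Abstract and the Primary outcome section say otherwise.

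A reader might infer three stronger things that the article does not support.

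- *That the GEE cannot isolate the 4-week effect.* It can, through the month-1 coefficient (Step 2). The article states neither how time is coded nor that an omnibus test will be used.
- *That baseline is ignored.* The Trial phase section plans comparison with baseline, and a group-by-time model that includes discharge compares change. Under randomisation that contrast is unbiased. Preferring baseline as a covariate is a matter of precision, and covariate choice alone may be left to an analysis plan.
- *That the omnibus terms are generally weak, or that the sample size was set for a 4-week comparison.* For a sustained effect both terms reach 81%, and for a 4-week-only effect the interaction does too. Since the programme runs for up to 12 months, a sustained effect is at least as plausible as a waning one. Sample size estimation gives no time point and does not name CHQ.

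A separate analysis plan may name the test. The point remains because the article does assign methods to outcomes, and that assignment contradicts its own primary outcome.

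**Conclusion.** The point holds as a contradiction between sections: under the Abstract and the Primary outcome section, the primary outcome has no assigned test. If CHQ is put through the GEE, no term is designated as decisive. This part rests on the text alone and needs no calculation.

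The figures show only that the designation matters. Under the stated assumptions, power for the 4-week question runs from 64% to 93% according to r and the handling of baseline, and the two omnibus terms can differ by 70 percentage points (81% against 11%). The effect size is back-solved, and the correlations and effect patterns are assumed. The gain from baseline adjustment is real but depends on r: at r = 0.5 it is 10 points over either alternative. The article does not support a claim that the planned GEE is invalid or that CHQ would go unanalysed.

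**What to change.** 1. State one primary outcome and time point, the same in the Abstract, the end of the Background, the Primary outcome section and Data analysis.
2. If it is CHQ at 4 weeks, name the primary test: the between-group difference in CHQ at 4 weeks adjusted for baseline CHQ, either by ANCOVA or as the 4-week contrast of the longitudinal model with baseline as a covariate, two-sided at 5%, with a 95% confidence interval. Report the 3-, 6- and 12-month contrasts and the omnibus GEE effects as secondary.
3. If it is readmission at 4 weeks, correct the Abstract and the Primary outcome section, and say that the sample size was derived for quality of life.
4. Record the decision with a date, before outcomes are compared between groups.

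The cost under item 2 is analysis wording only. The outcome measures are already scheduled at discharge and at 1 month, so no new data are needed.

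### The reason given for GEE does not address loss through death and decline: the 6- and 12-month contrasts may be biased, and how deaths are treated can change the PPS result

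*Protocol article*

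**What the plan says.** Data analysis assigns the method: "A generalized estimating equation (GEE) will be used to examine the group, time, and interaction effects on the secondary outcome variables". The only reason offered is: "The GEE is chosen because it treats observations of longitudinal data as correlated and thus is more robust in estimating standard errors". Measurements are taken "at discharge and at 1, 3, 6, and 12 months post-discharge" (Outcome measures). The primary quality-of-life measure is the "Chronic Heart Failure Questionnaire - Chinese version (CHQ) at 4 weeks post-discharge" (Primary outcome).

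The article itself describes a population in which many will not reach the later visits:

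- One of the four eligibility indicators, of which two are needed, is "patient thought to be in the last year of life" (Study settings and participants).
- The Background cites a 40 % "death rate within the first year after diagnosis" for heart failure.
- Secondary outcomes reports that the Edmonton Symptom Assessment System (ESAS), itself a trial outcome, independently predicts survival.
- Sample size estimation allows for 20 % attrition.

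For the PPS: "The level of physical performance is rated on a scale of 100 (normal) to 0 (death"). No value for death is given for the CHQ, MQOL-HK, ESAS or satisfaction scale.

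**The concern.** The article fixes a method and gives a reason for it, and the reason answers the wrong question. The sandwich variance makes the standard error trustworthy when the correlation is mis-specified. It does nothing to the point estimate when sicker patients stop contributing scores. If low scorers leave, and leave in different numbers by arm, the observed means at 6 and 12 months are compared between groups that have been selected differently.

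Death raises a second issue. After death a quality-of-life or symptom score does not exist; it is not a missing number. The article does not say which patients the later contrasts describe. Because the PPS alone has a death anchor, its analysis could count deaths as the worst score while the other scales leave them out. At stake are the 6- and 12-month results for function, symptoms and quality of life, and the comparison with baseline promised under Trial phase.

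**Working it through.** **1. The plan's own figures.** The article gives no figure for deaths, missing scores or bias. To set a scale: planning difference 60.4 − 52.3 = 8.1 (Sample size estimation). No SD is given. Solving 117 per arm, 80 % power and two-sided 0.05 backwards gives SD = 8.1 / [(1.960 + 0.842) × √(2/117)] = 22.1. This is circular and serves only as an input.

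**2. How much loss by death?** If the cited 40 % applied and the hazard were constant (both assumptions; the figure is for heart failure after diagnosis, not for this trial), the proportion dead at week t is 1 − 0.6^(t/52):

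- 4 weeks: 1 − 0.6^(4/52) = 3.9 %
- 6 months: 1 − 0.6^(26/52) = 22.5 %
- 12 months: 40 %

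**3. What GEE then estimates.** With group, time and interaction in the model and an independence working correlation, the fitted mean for each arm and visit is the mean of the scores observed there. The robust variance leaves that mean unchanged.

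**4. Same loss mechanism in both arms, true effect 8.1 at every visit.** Large-sample simulation, 200,000 per arm, loss depending on the last observed score. In the first setting SD is 22, correlation 0.6, and the odds of loss rise e-fold per SD lower score (44 % v 36 % lost at 12 months).

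| Visit | 1 mo | 3 mo | 6 mo | 12 mo |
|---|---|---|---|---|
| GEE, independence | 8.09 | 7.77 | 7.43 | 7.08 |
| Likelihood model | 8.12 | 8.14 | 8.13 | 8.17 |

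- The 12-month shortfall is 8.1 − 7.08 = 1.02, or 13 %. With half the slope it is 8.1 − 7.76 = 0.34.
- With SD 22.1, a slope of 0.7 per SD on the logit scale and 40 % control loss, bias is −0.5 with independence and about 0 to +0.1 with exchangeable correlation.
- Over the effect settings tried, the 12-month GEE estimate was about 6.9 to 7.8, a shortfall of 0.3 to 1.2. With the same mechanism and no true effect it was about 0.

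**5. Loss differing by arm, no true effect: bias at 12 months** (slope 0.7; negative is against HPHP).

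| Lost, control v HPHP | Loss depends on | Independence | Exchangeable |
|---|---|---|---|
| 40 % v 25 % | nothing (unrelated to score) | about 0 | about 0 |
| 40 % v 25 % | last observed score | −1.4 | −0.1 to +0.2 |
| 60 % v 20 % | last observed score | −4.0 | −0.1 to +0.8 |
| 40 % v 25 % | unseen current score | −1.8 to −1.9 | −0.6 to −1.0 |
| 60 % v 20 % | unseen current score | −5.0 to −5.5 | −2.0 to −2.4 |

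**6. Time effect.** With no true change, no treatment effect and one mechanism in both arms (40 % lost), independence GEE shows an apparent 12-month rise of 2.5 to 5.1 points, because low scorers leave.

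**7. Death versus other loss.** Steps 4 and 5 use as truth a score for every patient, including those lost. If all loss were death, the 6.9 to 7.8 of step 4 would be the true difference among survivors, and the likelihood model's value near 8.1 would extrapolate scores past death. The shortfall is a bias only for patients who are alive but not measured.

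**8. PPS.** Assume a survivor mean of 50 in both arms and deaths of 40 % v 30 %. Deaths left out: 50 − 50 = 0. Deaths scored 0: 0.70 × 50 − 0.60 × 50 = 35 − 30 = 5 points.

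**The case against.** Much of the case on the other side stands.

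- **The article is short and an analysis plan may exist.** Weighting, working correlation and missing-data rules are commonly left there, so their absence is no fault. This stands. What remains is that the article states a reason for its chosen method, and that reason does not meet the threat its own population presents.
- **A reader might infer that GEE is valid only under loss completely at random, so the later effects are biased.** The article does not support that. Loss depending on modelled covariates is allowed, and a suitable working correlation removes most of the bias when loss depends on observed scores. An independence structure is an assumption here, since none is named.
- **A reader might infer that deaths are handled inconsistently across scales.** No section says so. Zero on the PPS is an anchor of the instrument, not an analysis rule.
- **Switching to a mixed model for everyone would be worse if loss is mostly death.** Step 7 confirms this: such a model describes a population in which nobody dies. Nor does it cure loss depending on unseen scores.
- **The bias is small beside the sampling error.** With 140 per arm and 44 % v 36 % lost, about 78 and 90 remain, so the 12-month standard error is 22 × √(1/78 + 1/90) = 3.4, and a bias of 1.0 is about 0.3 standard errors. This is fair for a common mechanism, but not for the arm-dependent cases in step 5. It also rules out calling the 12-month results uninterpretable.
- **Scope.** GEE is assigned to secondary outcomes. The CHQ is primary under Primary outcome, whereas the Background calls readmission the key outcome, so it is unclear whether GEE covers the CHQ. It does cover the PPS, ESAS and satisfaction scale.

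**Conclusion.** The point holds in a limited form. The stated reason for GEE does not protect the 6- and 12-month contrasts from loss related to earlier scores. With an independence working correlation these contrasts may be biased: about 0 to −1.2 points of an 8.1-point effect at 12 months under a common mechanism, and in the illustrations as far as −4.0 to −5.5 when loss differs sharply by arm. The 4-week result is little affected (8.09 against 8.1). These sizes rest on assumed loss rates, slopes and correlations and on a back-solved SD; the article fixes none of them. They apply to loss of living patients, not to death.

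Separately, no rule for deaths is stated, and the choice matters for the PPS: 0 or 5 points in the example above. The change is worth making before analysis, but the point does not threaten the 4-week comparison.

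**What to change.** 1. Separate death from other missingness, and report deaths by arm and visit.
2. Define one target for every scale, including the PPS: patients alive at each visit, with no scores extrapolated past death.
3. For living patients with missing scores, use a likelihood-based repeated-measures model with baseline and arm by visit, drawing on it only for visits at which the patient was alive. Alternatively, keep GEE and weight it for dropout among those alive. State the assumed dropout mechanism either way.
4. Because survivors may differ by arm, add one prespecified sensitivity analysis in all randomised patients that gives death the worst rank on every scale.

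The cost is a change of analysis wording, slightly more modelling assumptions and one extra analysis. No further patients or measurements are needed. Under Trial status the article says data collection is at its final stage, so the change should be fixed before the data are analysed by arm. Loss depending on unseen scores would remain a limitation to acknowledge.
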